### Primary outcome measure

The proportion of families who report that they have a fire escape plan will be compared between treatment arms (IPB plus facilitation versus control and IPB only versus control) using random effects logistic regression to estimate odds ratios and 95% CI. The model will include randomisation stratum (trial site: Nottingham, Bristol, Norwich, Newcastle) as a fixed effect and will adjust for three cluster level variables (lead agency of the children’s centre (Local Authority, NHS or Voluntary sector led), Ofsted report scores for overall effectiveness and capacity for sustained improvement [29]) and two family level variables (having a fire escape plan at baseline and the Index of Multiple Deprivation (IMD) 2010 score [14]). These variables were selected as they are considered likely to be strongly associated with the outcome variable. The main comparisons will be between the IPB plus facilitation group versus control and the IPB only group versus control; a significance level of 0.05 will be used for each of these comparisons. Sub-group analyses will explore differential effects of the interventions by IMD, by adding interaction terms to the regression model. The intraclass correlation coefficient with a 95% CI will be estimated from the random effects regression model.

### Secondary outcome measures

#### Family level outcome measures

Binary secondary outcomes will be compared between treatment arms (IPB plus facilitation versus control and IPB only versus control) using random effects logistic regression and ordinal outcomes will be compared using random effects ordinal regression. Continuous outcomes will be compared using random effects linear regression, where assumptions are met. Where assumptions are not met, we will examine the distribution of the continuous outcome measure and categorise appropriately and analyse with ordinal or logistic models. Models will include randomisation stratum as a fixed effect and will also adjust for three cluster level variables (the lead agency of the children’s centre (Local Authority, NHS or Voluntary sector led [29]), and Ofsted report scores for overall effectiveness and capacity for sustained improvement) and two family level variables (baseline value of the secondary outcome measure, IMD).

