### Family participants

1. The proportion of families with a high level of fire escape planning behaviour (using a binary measure of fire escape plan behaviour derived from five component items using latent variable analysis. The component items are: having door keys accessible, having window lock keys accessible, having a torch beside the bed, knowing the sound of a smoke alarm and having exits clear.);

2. The proportion of families with smoke alarms fitted and working on every level of their home;

3. The proportion of families who report fire setting or match play by their children;

4. A bedtime fire safety routine score;

5. The proportion of families who have accessed smoking cessation services;

6. Number of correct responses to fire safety knowledge questions;

7. The proportion of families who were fairly satisfied or very satisfied with home safety information provided by children’s centres;

8. Implementation of the IPB assessed by:

a. The proportion of families who received advice on each of the 5 key messages in the IPB in the last year;

b. The proportion of families who attended a fire safety session in the last year;

c. The number of fire safety sessions attended by families in the last year;

d. The proportion of families who attended a fire safety session at a children’s centre in the last year;

e. The proportion of families who attended sessions about each of the 5 key messages in the IPB in the last year;

9. Families’ resource-use and expenditure in relation to fire safety practices.

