### Sample size

Eleven children’s centres per arm are required to detect an absolute difference in the percentage of families with a fire escape plan of 20% in either of the two intervention arms compared with the control arm. This assumes a control arm prevalence of 42% ascertained from a structured interview completed by families attending children’s centres in the four study centres [24], an intraclass correlation coefficient of 0.05, that outcomes are assessed on 20 families per children’s centre and is for 80% power and a 5% significance level (2-sided). This gives a total of 33 children’s centres. We will recruit a total of 36 children’s centres (9 per trial site), which will also allow for potential drop-out of one children’s centre per trial arm. Allowing for 33% loss to follow-up among families, 30 families per children’s centre will be recruited, a total of 1080 families.

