### Children’s centre level outcome measures

The proportion of children’s centres providing information and advice on fire prevention (the 5 fire safety messages from the IPB, see the background section for details) will be compared between the IPB plus facilitation arm and the control arm and the IPB only arm and the control arm using logistic regression. These analyses will adjust for stratum, the lead agency of the children’s centre and Ofsted report scores for overall effectiveness and capacity for sustained improvement [29].

The proportion of children’s centres using methods other than the IPB to promote fire safety will be compared between the IPB plus facilitation arm and the IPB only arm using logistic regression. This analysis will adjust for stratum, the lead agency of the children’s centre and Ofsted report scores for overall effectiveness and capacity for sustained improvement.

The number of fire safety sessions provided will be compared between the IPB plus facilitation and the control arm and between the IPB only and control arm using linear regression if assumptions are met. Where assumptions are not met, we will examine the distribution of the number of fire safety sessions provided and categorise appropriately and analyse with ordinal or logistic models. These analyses will adjust for stratum, the lead agency of the children’s centre and Ofsted report scores for overall effectiveness and capacity for sustained improvement.

Barriers and facilitators to children’s centres implementing the IPB will be coded and categorised and described for the IPB plus facilitation and IPB only arms.

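### The only stated fallback for non-normal secondary scores and counts is to categorise them, which discards information that ordinal or count models on the full values would keep

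*Protocol article*

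**What the plan says.** Under Family level outcome measures, the first-line rule is "Continuous outcomes will be compared using random effects linear regression, where assumptions are met". When those assumptions fail, the text reads "we will examine the distribution of the continuous outcome measure and categorise appropriately and analyse with ordinal or logistic models". No other fallback is named. The same paragraph assigns random effects ordinal regression to ordinal outcomes, without any grouping step.

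Three outcomes listed under Family participants could fall under the rule:
- item 4: "A bedtime fire safety routine score"
- item 6: "Number of correct responses to fire safety knowledge questions"
- item 8c: "The number of fire safety sessions attended by families in the last year"

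Under Children’s centre level outcome measures the rule recurs for sessions provided, after ordinary linear regression: "we will examine the distribution of the number of fire safety sessions provided and categorise appropriately and analyse with ordinal or logistic models".

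The Analysis section bases significance on likelihood ratio tests and says that analyses are done blind to arm.

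**The concern.** Non-normality is not a reason to group an outcome. A cumulative-logit model needs only the order of the values, so it can use every distinct score. A session count has its own family of models. Grouping first treats different values as equal, and the information lost cannot be recovered by the model fitted afterwards. Because the fallback includes logistic models, a two-group version is within the rule.

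These outcomes matter for interpretation. Knowledge and bedtime routine describe the behaviour change that the intervention aims at, and sessions attended is listed as a measure of implementation of the briefing. They help to explain a positive or a null primary result. The trial is sized on the primary outcome alone, with about a dozen centres per arm, so precision on these measures is worth keeping.

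**Working it through.** **1. The plan's own figure.** Inputs from Sample size: 42% in control, 20 points difference (so 62%), ICC 0.05, 20 families per centre, 80% power, 5% two-sided.
- Two-proportion formula: 97 per arm without continuity correction, 107 with it.
- Design effect: 1 + (20 − 1) × 0.05 = 1.95.
- Centres per arm: 97 × 1.95 / 20 = 9.46, or 107 × 1.95 / 20 = 10.43. The corrected version rounds up to the stated 11.
- Recruitment: 20 / (1 − 0.33) = 29.9, so 30 per centre; 36 × 30 = 1080.

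The stated numbers reproduce. No power is stated for the secondary scores or counts.

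**2. Clustered simulation.** Assumptions, none of them in the document: 12 centres per arm (36 / 3), 20 families each, centre-level t-test at 5%, 4000 replicates. It was run twice with assumed distributions.

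| Assumed outcome | Uncollapsed | Three groups | Two groups |
|---|---|---|---|
| 0–10 score with ceiling, latent ICC 0.05, 0.37 SD effect, run 1 | 77% | 74% | 68–69% |
| Same, run 2 | 78% | 74% | 64–68% |
| Overdispersed count, control mean 0.5, rate ratio 1.9, run 1 | 78% | – | 69% |
| Same, run 2 | 84% | – | 74% |

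The loss on the score is 3 to 4 points with three groups. With two groups it is 8 to 14 points on the score and 9 to 10 on the count, so about 10 overall. Rejection under no effect was 4.4% to 5.5%.

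**3. Sensitivity to the assumed shape.** A simpler simulation used 113 independent families per arm (effective size 11 × 20 / 1.95 = 112.8) and a rank test.

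| Assumed outcome | Uncollapsed | Three groups | Two groups |
|---|---|---|---|
| Count, means 0.5 v 0.85 | 62% | 60% | 49% |
| Count, means 2 v 3.2 | 73% | 53% | 35% |
| Skewed 0–10 score | 88% | 82% | 73% |

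The direction is the same throughout. The size is not stable: three groups cost from 2 points (a count mostly 0 or 1) to 20 points (a count with a long spread).

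**4. Normal-theory benchmark.** For a normal score, the efficiency of k groups is the sum over groups of (difference in normal density at the cut-points)² / (group probability). A median split gives 2/π = 0.64 and tertiles give 0.79. If the uncollapsed analysis had 80% power (standardised difference 0.373, effective size 112.8 per arm), power would be 61% and 70%. This calculation is for a normal outcome and holds the design effect fixed, so it is not used to size the point.

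**The case against.** The strongest reply is that the rule is conditional and mild. Linear regression comes first. The fallback names ordinal models and sets no number of groups, so keeping every score value and merging only sparse tails would comply with it. The bedtime and knowledge scores are not labelled continuous, so they could be handled as ordinal outcomes from the start and left uncollapsed. Ordinal and logistic models are valid choices, and any versus no attendance is already a separate outcome (item 8b). All of this is fair. It limits the point to what the text permits and does not show that a median split is planned.

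A reader might infer that the fallback will usually become the actual analysis. The document gives no item counts, score ranges, ceiling effects or proportions of zeros, so that cannot be shown. A reader might also take the normal-theory losses as the expected loss, but the rule is triggered when linear-model assumptions fail, which is where those figures least apply. Nor can the absence of cut-points be held against the article: an analysis plan that is not shown may fix them, and analysis blind to arm limits selective choice of a cut.

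What remains is that grouping is a stated method, the only one offered, and an analysis plan that follows the text would carry it out. Blinding does not restore discarded information.

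**Conclusion.** The point holds as an inexpensive improvement to secondary analyses. The text makes categorisation the sole fallback and allows collapse to two groups, when models on the full values are available and one of them is already in the plan. Under the clustered assumptions the loss is about 3 to 4 points of power on a score with three groups, and about 10 on a score or count with two. Other assumed shapes give smaller or larger losses, and with many categories the loss is slight. The unadjusted centre-level test used for these figures is simpler than the planned adjusted random-effects model, which is a further reason to read them as illustrative. The document does not support a claim that these outcomes will be dichotomised, that the results will be biased, or that the sample size or primary analysis is affected.

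**What to change.** Replace the categorising clause in both places.
- Bedtime and knowledge scores: random-effects ordinal regression on the uncollapsed values, merging only sparse adjacent values.
- Sessions attended by families: random-effects negative binomial regression, or random-effects ordinal regression on the uncollapsed count.
- Sessions provided by centres: the same models without the random effect.

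Keep the stratum and covariate adjustment already listed. These models are likelihood-based, so the likelihood ratio tests in the Analysis section still apply. Poisson regression with robust standard errors would not fit those tests and is better avoided here.

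The cost is a sentence in each of two sections, with no new data or sample. Random-effects ordinal regression is already planned, and the other models are available in Stata. The price is a proportional-odds or count-distribution assumption that has to be checked, and an effect measure (cumulative odds ratio or rate ratio) slightly less simple than a two-category odds ratio.

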### Children’s centre level outcome measures

The proportion of children’s centres providing information and advice on fire prevention (the 5 fire safety messages from the IPB, see the background section for details) will be compared between the IPB plus facilitation arm and the control arm and the IPB only arm and the control arm using logistic regression. These analyses will adjust for stratum, the lead agency of the children’s centre and Ofsted report scores for overall effectiveness and capacity for sustained improvement [29].

The proportion of children’s centres using methods other than the IPB to promote fire safety will be compared between the IPB plus facilitation arm and the IPB only arm using logistic regression. This analysis will adjust for stratum, the lead agency of the children’s centre and Ofsted report scores for overall effectiveness and capacity for sustained improvement.

The number of fire safety sessions provided will be compared between the IPB plus facilitation and the control arm and between the IPB only and control arm using linear regression if assumptions are met. Where assumptions are not met, we will examine the distribution of the number of fire safety sessions provided and categorise appropriately and analyse with ordinal or logistic models. These analyses will adjust for stratum, the lead agency of the children’s centre and Ofsted report scores for overall effectiveness and capacity for sustained improvement.

Barriers and facilitators to children’s centres implementing the IPB will be coded and categorised and described for the IPB plus facilitation and IPB only arms.

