### Ascertaining children’s centre outcomes

Information will be collected from children’s centres managers or staff on the promotion of fire prevention using a postal questionnaire at baseline and post intervention in the IPB plus facilitation arm and the IPB only arm, and at baseline and 12 months post randomisation in the control arm. Questions will be based on those used in a national survey of injury prevention activity amongst children’s centres in England [28]. Questions concerning resource use related to implementing the IPB will be included in the post-intervention questionnaire for all arms of the trial. The baseline questionnaire was piloted on 10 children’s centres across England who were not selected to take part in the trial and minor modifications were made.

During the intervention period, data on process measures such as the number of fire prevention sessions provided by the children’s centre, number of centres with a written plan for implementing the IPB, number of staff trained in delivering the IPB per centre, number of specific fire safety sessions from the IPB provided for parents and number and type of other methods used by each centre to reach parents with fire safety messages (e.g. home visits by outreach workers, incorporation of fire safety messages in existing activities) will be ascertained from the IPB plus facilitation arm through the facilitation contacts questionnaire and interviews and the activity logs.

Post-intervention, information on the implementation of the IPB will be ascertained from an implementation fidelity questionnaire and from implementation fidelity interviews, with centre managers and/or staff responsible for the delivery of the IPB in the IPB plus facilitation and the IPB only arms of the trial. The questionnaire and interview schedule will be based on the Carroll framework [21], on the review of the literature on the implementation and facilitation of health promotion interventions undertaken for the trial, the systematic review of barriers and facilitators to home injury prevention [11] and findings from interviews of children’s centre managers and staff described above. Data collected from the range of outcome measurement tools will be mapped onto the PARIHS framework [20] (described above) to explore the success of the implementation process.

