### Randomisation

Once 30 families have been recruited at a children’s centre, centres will be stratified by trial site (4 strata: Nottingham, Bristol, Norwich, Newcastle) and randomly allocated within strata to one of three arms using permuted block randomisation, with a block size of 3. The allocation schedule will be produced by an independent statistician, using the randomisation algorithm in Stata. These lists will be provided to an independent administrator who will prepare sequentially numbered opaque envelopes (one set for each of the four trial coordinating centres) with these allocations.

Children’s centres will be randomised in trios, once each stratum contains 3 children’s centres. In this way, allocation will be concealed from the children’s centres and the researchers up to the point of actually randomising a trio of centres. Once a stratum contains 3 children’s centres, the administrator will open the envelopes for each block of 3 children’s centres, record the allocations and notify each of the trial coordinating centres of the allocation. Children’s centres will then be notified of their allocation by email.

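### The two binary centre-level outcomes are to be fitted with 9 to 12 parameters on 22 to 36 centres, and the planned likelihood ratio test does not hold its 5% level

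*Protocol article*

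**What the plan says.** Two binary outcomes are analysed at centre level (Protocol article, Children's centre level outcome measures). The first is whether a centre gives advice on the five fire safety messages. Each intervention arm is compared with control, ending with "the IPB only arm and the control arm using logistic regression". The second is whether a centre promotes fire safety by means outside the IPB, which "will be compared between the IPB plus facilitation arm and the IPB only arm using logistic regression".

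Both models adjust for randomisation stratum, the centre's lead agency and two Ofsted ratings, one of overall effectiveness and one of the capacity to keep improving. The Analysis section sets likelihood ratio tests with p below 0.05 for all outcomes. No penalised, exact or reduced model is named for a logistic fit that fails.

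The number of sessions goes to linear regression first. Only if its assumptions fail will the analysts "categorise appropriately and analyse with ordinal or logistic models".

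On numbers, the Sample size section states "We will recruit a total of 36 children’s centres (9 per trial site") and allows for losing one centre per arm. Centre activity is collected in every arm "using a postal questionnaire at baseline and post intervention" (12 months after randomisation in the control arm), but the centre-level models do not use the baseline answer. The family-level secondary models do adjust for baseline.

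**The concern.** Each centre supplies one yes or no. The chi-squared approximation to the likelihood ratio statistic needs many more events and non-events than parameters, and here there are at most about two per parameter. Two things follow. The test rejects too often when nothing has changed. Some fits also separate, meaning that a combination of covariates predicts the outcome perfectly and at least one coefficient runs to infinity. These outcomes bear on whether the IPB changed what centres do, so a false positive here would be read as evidence of implementation. The scarce degrees of freedom go to lead agency and Ofsted scores, while the centre's own baseline provision, already collected, is left out.

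**Working it through.** **The plan's own figure.** The article gives no power for centre-level outcomes; the number of centres comes from the primary outcome. For 42% against 62%, 80% power and two-sided 5%, the usual two-proportion formula gives 97 families per arm, or 107 with continuity correction. The design effect is 1 + 19 × 0.05 = 1.95. Then 107 × 1.95 = 208.65, and 208.65 / 20 = 10.43, rounded up to 11 centres. This reproduces the stated 11 per arm.

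**Parameter count.** Randomisation is "stratified by trial site (4 strata: Nottingham, Bristol, Norwich, Newcastle"), so site takes 3 terms. The primary analysis text defines "lead agency of the children’s centre (Local Authority, NHS or Voluntary sector led"), so lead agency takes 2. The two Ofsted scores take 2 terms if linear, or 4 if each has three categories (an assumption, as the coding is not stated).

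| Model | Parameters with intercept | Centres | Centres per parameter |
|---|---|---|---|
| Three arms, linear Ofsted | 1+2+3+2+2 = 10 | 33–36 | 3.3–3.6 |
| Three arms, categorical Ofsted | 1+2+3+2+4 = 12 | 33–36 | 2.8–3.0 |
| Two arms, linear Ofsted | 1+1+3+2+2 = 9 | 22–24 | 2.4–2.7 |
| Two arms, categorical Ofsted | 1+1+3+2+4 = 11 | 22–24 | 2.0–2.2 |

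At 50% prevalence, the most favourable case, events per non-intercept parameter run from 16.5/11 = 1.5 to 18/9 = 2.0 with three arms, and from 11/10 = 1.1 to 12/8 = 1.5 with two.

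**Test level under no effect.** The stated model and test were simulated with no arm or covariate effect. Assumptions not in the article: prevalence 50–90%, lead agency split 60/20/20 or equally, three-level correlated Ofsted scores. All data sets with a non-constant outcome count, including separated ones, since the likelihood ratio statistic stays finite there.

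- Three-arm fits: rejection about 10–18%.
- Two-arm fits: rejection about 12–24%.
- The lowest result, 10%, came from 36 centres, linear Ofsted, 50% prevalence and equal lead-agency groups, with 300 replicates. Its standard error is √(0.10 × 0.90 / 300) = 1.7 points, so it is still clear of 5%.
- Restricted to fits without separation, a further set of runs gave 7–11% (three arms) and 8–15% (two arms).

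**Any separation.** With the 60/20/20 split and linear Ofsted, three-arm fits separated in 17–26% at 50% prevalence, 39–48% at 70%, 69–75% at 80% and 96–97% at 90%. Two-arm fits separated in 60% or more. With equal lead-agency groups and 50% prevalence, the linear rates fell to 10% (three arms, 36 centres) and 43% (two arms, 24 centres).

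**Separation reaching the arm term.** Further runs (about 500 replicates, 12 centres per arm, three arms) separated the two questions for the IPB plus facilitation term. Each cell gives linear / categorical Ofsted.

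| Prevalence (control / IPB / IPB plus facilitation) | Any separation | Arm term affected |
|---|---|---|
| 50% throughout | 10% / 29% | 0% / 4% |
| 70% throughout | 37% / 52% | 5% / 11% |
| 40 / 60 / 75% | 20% / 36% | 7% / 12% |
| 60 / 80 / 95% | 78% / 92% | 60% / 71% |

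In two-arm fits the arm term was affected in 9% / 30% at 50% prevalence and 26% / 45% at 70%.

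**Does a change of method cure it?** Two arms, 24 centres, no effect, 1500 replicates; type I error at nominal 5%:

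| Method | 50% | 70% | 80% | 90% |
|---|---|---|---|---|
| Ordinary logistic, arm + site | 6.8% | 10.2% | 9.1% | 7.6% |
| Firth, arm + site + baseline | 4.5% | 4.9% | 3.2% | 1.9% |
| Exact test stratified by site | 1.7% | 2.3% | 0.9% | 0.1% |

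Dropping covariates alone is not enough: ordinary logistic regression on arm and site still separated in 13%, 40%, 72% and 95%.

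**The case against.** A reader might infer that most fits will separate and that the analysis will usually return no usable estimate. The article does not support that. It gives no provision rate, and near-universal provision in the IPB arms is not implied: the outcome concerns five messages, and the delivery section foresees centres that cannot cover them all. The facilitation section plans an extra contact where nothing has moved by month 3. Separation on a sparse lead-agency or Ofsted level also leaves the arm coefficient finite and testable. In the three-arm runs that tracked it, the arm estimate was lost in a majority of fits only with 95% provision in one arm. This part of the objection stands.

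It is also fair that session counts go to linear regression first. A reader might want to put a power cost on categorising them, but the article does not say how categories would be cut, so no figure can be derived. Adding the baseline value to the full covariate set would worsen the overfitting, and for methods outside the IPB no pre-IPB equivalent is defined.

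Finally, Ofsted coding and sparse cells are commonly settled in an analysis plan. But the model, the covariates and the test are fixed in this article, and the level was exceeded under every coding tried.

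**Conclusion.** The point holds for the two binary centre-level outcomes. As written, the nominal 5% test runs at about two to just under five times its level (10/5 = 2; 24/5 = 4.8) under the assumed covariate distributions. The excess appeared in every null scenario, so it does not depend on high prevalence. Separation is a second, less predictable problem: about 10–20% of fits in the most favourable three-arm case, a majority of two-arm fits in most scenarios, and an infinite arm odds ratio in only some of these. Those rates rest on prevalence, covariate mix and Ofsted coding, none of which the article gives. If each comparison with control is fitted on its own two arms, the two-arm figures apply there too. These are secondary outcomes; the primary analysis is not touched.

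**What to change.** For these two outcomes, drop lead agency and both Ofsted scores. Fit Firth-penalised logistic regression, with penalised-likelihood tests and confidence intervals, on arm and site. For provision of advice, add the centre's own provision from the baseline questionnaire. The advice model then has 1+2+3+1 = 7 parameters with three arms. The comparison of the two IPB arms on other methods has 1+1+3 = 5. Report raw proportions by arm with exact confidence intervals. Keep a site-stratified exact test as a sensitivity analysis only, since it is valid but very conservative. Use the same penalised, reduced model if session counts reach the logistic fallback.

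This changes analysis wording only and needs no new data. The cost is that lead agency and Ofsted scores are no longer adjusted for in these secondary analyses, and the penalised test is itself somewhat conservative at high prevalence (1.9% at 90%). The penalised model was checked for two arms of 12 centres, with a baseline term unrelated to the outcome; the three-arm version and the version without baseline were not simulated.
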